### 3.2.3 Appointment booking and additional information given to the participant (intervention arm)

Prior to patient discharge, an appointment will be made at the clinic. Participants will be provided with additional information on clinic location through a brochure (see section 8.8) prior to discharge. The brochure will also contain a reminder of the time of their appointment. The Monarch Clinic will be found at Harmony Medical Centre, [name], located south-west of downtown, a 15 minute drive from

the Civic campus and 20 minutes from the General campus. The Harmony Clinic has abundant parking (free on the street or a small fee inside the associated lot) and is fully accessible.

### **3.3 Non-intervention arm post-discharge events**

Women randomly assigned to the non-intervention arm option will be discharged according to the current hospital standards, in accordance with their physician or midwife's decision. After hospital discharge, the participant and her baby will be entitled to receive follow-up care and seek breastfeeding support that is currently available in the community (e.g. through their family doctor, Public Health Unit or private services), but may not attend the pilot breastfeeding clinic.

Women will be contacted at 2 weeks, 1 month and 3 months post-delivery to complete the different surveys and questionnaires (3.5).

As is current standard of care practice, women will be assessed by Public Health Nurses for post-partum depression shortly after birth. Services will be provided as per the standard.

As part of the research, women will be contacted by phone at 3 weeks by a Public Health Nurse to administer the Edinburgh Postnatal Depression Scale. In the event of a high score, the Ottawa Public Health Nurse will provide the participant with appropriate support. Information collected will be abstracted by the research staff.

### **3.4 Intervention arm post-discharge events**

Women randomly assigned to the intervention will be discharged approximately 24 hours following a vaginal delivery or approximately 48 hours following a C-section. While this is the aimed ideal time of discharge, there may be variation as time of discharge will ultimately depend on the attending physician/midwife's opinion/orders and what he/she feels is in the best interest of the mother and her newborn. Women who choose to stay in the hospital longer will still be referred to the Monarch Clinic and will not be excluded from the study.

Women and their infants will be expected to attend a pre-booked appointment at the breastfeeding clinic, scheduled within 48 hours of their discharge. Clinic staff will follow up with the participant if she fails to keep the mandatory follow-up appointment. This first appointment will include maternal assessment and care (e.g., wound care, prescriptions), neonatal care (e.g., tongue-tie clips, jaundice screening using transcutaneous bilirubinometer), blood work including TSB (samples couriered to TOH central laboratory, HBHC postpartum assessment, and breastfeeding assessment and support. Family physicians will be available for on-site consultations in the mornings, and lactation consultants and registered nurses will be at the clinic throughout the day from Monday to Friday and Saturday mornings. Medical data (e.g., bilirubin level (transcutaneous and serum), newborn assessment, infant weight gain, urination and defecation frequency, breastfeeding assessment and progress, maternal care) found in the clinic chart will be gathered.

The Bilirubin Pathway, established by the CMNRP, will be used to guide for the management of neonatal jaundice. Those guidelines provide recommendation for subsequent TSB and or TCB follow-up, according to the modified Buthani's normogram and whether risk factors for hyperbilirubinemia are

present or not. For babies discharged before 24 hours, blood for the newborn screening will be drawn at the first visit and sent by mail to the Newborn Screening Ontario laboratory located at CHEO.

Additional follow-up visits at the breastfeeding clinic will be made available to participants for the month following the birth of their baby.

Participants in the intervention group will also be contacted at 2 weeks, 1 month and 3 months to complete the different surveys and questionnaires (3.5).

Women will be assessed by a Public Health Nurse for post-partum depression in the clinic. Services will be provided as per the standard.

As part of the research, women will be contacted by phone at 3 weeks by a nurse from Ottawa Public Health to administer the Edinburgh Postnatal Depression Scale. In the event of a high score, the Ottawa Public Health Nurse will provide the participant with appropriate support. Information collected will be abstracted by the research staff.

### 3.5 Follow-up surveys at 2 weeks, 1 month, 3 months and 6 months after hospital discharge

Participants will be contacted by email or by phone to complete the following:

- At 2 weeks:
  - **A questionnaire assessing breastfeeding complications**, developed for this study
  - **Breastfeeding Self Efficacy Scale (BSES-SF)**. This is a 14-item self-report instrument developed to measure breastfeeding confidence 
  - A questionnaire to assess the **access to community resources**, the rate of readmission of the babies and the level of satisfaction of mothers with the breastfeeding support received.
  - A questionnaire to determine the **rate of exclusive breastfeeding**. Participants will be asked to answer question on the methods used to feed their babies in the past 24 h hours and in the past two weeks. Exclusive breastfeeding will be as defined as the feeding of only the infant's mother's milk for at least 2 weeks prior to collected outcome.
- At 3 weeks only (by phone by a nurse from Ottawa Public Health)
  - **Edinburgh Postnatal Depression Scale**. This is a 10-item screening tool to identify postpartum depression at the time of its administration . A score of 13 or higher on the EPDS is considered indicative of postpartum depression and a score of 10 to 12 is indicative of being at risk for postpartum depression (see section 3.6).
- At 1 month:
  - **Breastfeeding Self Efficacy Scale (BSES-SF)**. This is a 14-item self-report instrument developed to measure breastfeeding confidence 

- A questionnaire to assess the **access to community resources**, the rate of readmission of the babies and the level of satisfaction of mothers with the breastfeeding support received.
  - A questionnaire to determine the **rate of exclusive breastfeeding**. Participants will be asked to answer question on the methods used to feed their babies in the past 24 h pours and in the past two weeks. Exclusive breastfeeding will be as defined as the feeding of only the infant's mother's milk for at least 2 weeks prior to collected outcome.
  - **Socio-demographics survey**. This survey was developed using questions and categories used in the Public Health Agency of Canada survey “What Mothers Say: The Canadian Maternity Experiences “
- At 3 months:
    - **Breastfeeding Self Efficacy Scale** (BSES-SF). This is a 14-item self-report instrument developed to measure breastfeeding confidence
    - A questionnaire to assess the **access to community resources**, the rate of readmission of the babies and the level of satisfaction of mothers with the breastfeeding support received.
    - A questionnaire determine the **rate of exclusive breastfeeding**. Participants will be asked to answer question on the methods used to feed their babies in the past 24 h pours and in the past two weeks. Exclusive breastfeeding will be as defined as the feeding of only the infant's mother's milk for at least 2 weeks prior to collected outcome.
    - **Mother Satisfaction Survey** (developed for this study).
  - At 6 months:
    - Follow-up survey: A very short survey (5 minutes) to determine breastfeeding habits at 6 months.

All surveys (in French and English) are included in section 8 (the surveys are the same as the ones used in the pilot study, except for the addition of the Mother Satisfaction Survey). Participants will be offered the possibility to complete the follow-up surveys online. The master study log will include the name of the participant, their full contact information including email address, and their study ID number. The links to the online questionnaires, instructions and login information will be sent by email (to participants who provide their email address) at 15 days, 1 month, 3 months and 6 months. If the participants do not complete the questionnaires within 2 days, we will send them a reminder by email. Offering to complete the questionnaires online will give flexibility to the participants providing them with the opportunity to complete the survey at their own pace. Participants will have the ability to save their answers without completing the totality of the survey and return to the questionnaire later, for extra flexibility given the unpredictable nature of a mother’s schedule.

Participants will also be offered the option to be contacted over the phone by the research staff to complete the survey, as some may not have internet access or be comfortable answering an electronic

survey. The entire phone interview should take approximately 40 minutes at each contact. Recognizing that the first few weeks after returning home with a newborn can be overwhelming for the mother, the interview may be done in multiple shorter sessions, at the mother's discretion, to accommodate her.

In the event of a high score on the Edinburgh Postnatal Depression Scale (indicating possible mood disorder), the Ottawa Public Health Nurse will provide the participant with appropriate support and referrals.

**The anticipated duration of the study is 11 months, and ends with the completion of the last set of surveys (5 months of recruitment + 6 months of follow-up).**

### 3.6 Risks and risk management

There is no anticipated risk to the participant or her baby for participating in this trial. In the event that participants or their babies become ill or experience difficulties prior to their scheduled appointment at the clinic, they will be reminded to go to the emergency department of consult with their family doctor, and not wait for the appointment if they feel the problem is urgent. Given that hospital discharge 24 hours after vaginal delivery and 48 hours after C-section is not an uncommon practice in hospital settings, we feel that the risks for this study are low.

In the event that a participant randomized to the intervention group needs to stay in hospital longer than anticipated, due to their attending physician's decision, she will still have access to the postpartum clinic post discharge. Participants will be analyzed as "intent to treat" events.

As stated in the Information and Consent Form, participants can decline answering any question.

### 3.7 Criteria for removal/withdrawal from the study

Participants may decide to withdraw from the study at any time point in the study. A participant may be removed from the study if the baby or the mother becomes gravely ill and needs intensive care or if the attending physician feels that it is in the best interest for the mother and baby not to continue with the study. If withdrawn for the study, the researcher will still use the data already collected from the participant unless she asks for it to be destroyed. No new information will be collected.

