## 2.4 Secondary Outcomes

1. Rates of hyperbilirubinemia requiring phototherapy or hospitalization
2. Poor infant weight gain requiring intervention (pumping, supplementation, hospitalization)
3. Incidence of breastfeeding difficulties (e.g., sore nipples, insufficient milk supply, inadequate latch, engorgement)
4. Breastfeeding self efficacy score (Breastfeeding Self Efficacy Scale or BSES) at 2 weeks, 1 month and 3 months
5. Score of the Edinburgh Post-partum Depression Scale for new mothers
6. Access to community-based services: Public Health Clinics, Family Doctor, Pediatrician
7. Number of emergency department visits for the mother and the baby
8. Number of hospital readmissions for the mother and her baby
9. Mothers' satisfaction with the support received
10. Length of stay in the hospital, from delivery to discharge
11. Costs associated with this community-based postpartum clinic.

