## 4 Statistics

### 4.1 Sample size

Based on an estimated 50% rate of exclusive breastfeeding at 3 months in the control group, 200 patients per group will be needed to detect a 15% relative difference in the intervention group ( $\alpha=0.05$ ,  $\beta=0.9$ , one-sided test). Assuming an attrition rate of 15% (i.e. loss to follow up, unsuitability, or other unanticipated events), we set a target of **230 participants per group** making a total of **460** women. Accounting for the logistical concern of making full use of the nursing staff, lactation consultants, and family physicians at the clinic, we decided to apply a 1:2 ratio for control to intervention allocations and determined that 154 and 306 patients are needed for the control and intervention groups respectively (maintaining significance level, power, and effect size).

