### 4.3 Statistical analysis

All outcomes will be analyzed based on the intention-to-treat principle, in accordance with the randomization allocations described previously. The primary goal of this study is to test the hypothesis that rates of exclusive breastfeeding at 3 months (defined as the feeding of only the infant's mother's milk for at least 2 weeks prior to collected outcome) will be higher in the group of women attending the post-partum clinic, as compared to those under standard of care. For comparison between intervention and control arms we will employ a generalized estimating equation multivariable regression model to account for prognostic risk factors that have not been sufficiently balanced by randomization. Group and individual level covariates will be included in the model, with recruitment site as the clustering unit to allow for inference at the individual level. This design will also investigate the effect of demographic

drivers such as maternal age, education, parity, etc., on the primary outcome, producing both crude and adjusted risk estimates and their 95% confidence intervals.

Secondary outcomes will be collected by studying the medical data (such as rates of hyperbilirubinemia and self-efficacy) that will be entered in the database by the research staff. This data will be compared across case and control groups using the Pearson Chi-squared, Student's t, or Fisher's exact test, depending on their observed frequencies. We will also compare the statistics and outcomes from the present study with baseline estimates from phase 1. The answers women provide through their questionnaires and surveys will be the main instruments for determining exclusive breastfeeding rates and their behavioral and emotional measurements. For the cost-effectiveness analysis, direct and indirect costs for the intervention and control groups will be compared regarding use of resources (e.g., clinic visits, physician visits, Emergency Department visits, hospital readmission, and indirect cost).

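### Section 3.7 ends data collection for dyads removed for grave illness or on a physician's judgement, which creates avoidable outcome-related missing data in a trial that promises intention-to-treat

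*Protocol*

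**What the plan says.** Section 3.7 of the protocol gives three ways out of the study. A mother may withdraw at any time. The study may act on illness: "A participant may be removed from the study if the baby or the mother becomes gravely ill and needs intensive care". A removal may also follow "if the attending physician feels that it is in the best interest for the mother and baby not to continue with the study". One data rule then covers the section: "the researcher will still use the data already collected from the participant unless she asks for it to be destroyed", followed by "No new information will be collected".

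Section 4.3 states that "All outcomes will be analyzed based on the intention-to-treat principle, in accordance with the randomization allocations described previously", and section 3.6 repeats the principle for women who stay in hospital longer than planned. Section 2.4 lists among the secondary outcomes "Number of hospital readmissions for the mother and her baby", together with emergency visits for both, jaundice leading to treatment or admission, length of stay, and costs. Section 2.2 hypothesises fewer emergency visits and readmissions with the clinic. Section 6.1 has the principal investigators review every readmission in the first 15 days after discharge and send a count to the data safety monitoring board after each 200 enrolments.

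**The concern.** Two different events share one data rule. When a mother withdraws consent for her data, collection has to stop. When the study or a physician removes a dyad, nothing in the protocol requires outcome collection to stop, yet 3.7 stops it.

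These removals come after randomisation. They are optional, and no criteria are given beyond those quoted. The protocol conceals allocation only until enrolment: section 3.2.2 has staff tell the woman her arm, and no blinding of care is described afterwards, so the trial is in effect open-label. The trigger is close to what is being measured. The clinic arm is aimed at early discharge, so serious illness afterwards is both a safety question and part of the readmission and cost comparison. The resulting gaps may depend on outcome and on arm. An analysis plan can say how to treat missing values, but it cannot recover data that the protocol forbids staff to collect.

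**Working it through.** The protocol states no figure for this point, so the check is first of the text and then an illustration on assumed rates.

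**Step 1. What a removed dyad loses.**

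| Item | Source in the protocol | After a removal under 3.7 |
|---|---|---|
| 3-month exclusive breastfeeding | Survey (3.5; day 84 in 3.8) | Not collected |
| Infant readmission, use of resources | Surveys at 2 weeks, 1 month, 3 months (3.5, 3.8) | Not collected; if removal comes before day 14, no survey has yet recorded anything |
| Clinic chart data | Clinic arm only (3.8) | Earlier data kept, so what survives differs by arm |
| Readmission within 15 days | Investigator review and board count (6.1) | Not stated; read literally, 3.7 bars gathering it after removal |
| Administrative linkage | Health number recorded for possible later use (3.2.1) | Not tied to any trial outcome |

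**Step 2. Primary outcome.** Input from 4.1: 50% exclusive breastfeeding in controls. Assumptions, not in the protocol: true rate 50% in both arms, no removed dyad exclusively breastfeeding, and removed dyads left out of the calculation. With removed share r, observed rate = 0.50/(1 − r).

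- Clinic, r = 3%: 0.50/0.97 = 51.5%.
- Control, r = 1%: 0.50/0.99 = 50.5%.
- Spurious difference: 1.0 point.

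Range: 1% in both arms gives 0. Clinic 2% against control 1% gives 51.0 − 50.5 = 0.5 points. Clinic 5% against control 1% gives 0.50/0.95 = 52.6%, so 2.1 points. Clinic 1% against control 3% gives −1.0 point.

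For scale, with 306 and 154 women the standard error of the difference is √(0.25/306 + 0.25/154) = 4.9 points.

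The counting rule matters about as much. Suppose 50% of the remaining women in each arm breastfeed exclusively, and k removed clinic women (none in control) are counted as not doing so instead of being left out. The difference moves by 0.50 × (306 − k)/306 − 0.50: −0.5 points for k = 3 and −1.5 points for k = 9.

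**Step 3. Readmissions.** Inputs from 4.1: 154 control, 306 intervention. Assumptions: true readmission risk 5% in both arms (7.7 and 15.3 cases), or 4% against 6% (6.2 and 18.4 cases); f = share of readmitted cases removed before being recorded. If they also leave the denominator, observed risk = e(1 − f)/(n − e·f), where e is the number of cases. If they stay in it, the observed ratio = true ratio × (1 − f in intervention)/(1 − f in control).

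| f control / intervention | True ratio 1.00: left out / kept in denominator | True ratio 1.50: left out / kept in denominator |
|---|---|---|
| 10% / 10% | 1.00 / 1.00 | 1.50 / 1.50 |
| 0% / 10% | 0.90 / 0.90 | 1.36 / 1.35 |
| 10% / 30% | 0.79 / 0.78 | 1.18 / 1.17 |
| 0% / 30% | 0.71 / 0.70 | 1.07 / 1.05 |

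Worked example, 10%/30% at 5%, left out: control (7.7 × 0.9)/(154 − 0.77) = 4.52%; intervention (15.3 × 0.7)/(306 − 4.59) = 3.55%; ratio 0.79.

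The 30% rows correspond to 0.30 × 15.3 = 4.6 or 0.30 × 18.4 = 5.5 unrecorded cases in the clinic arm. The two denominators give almost the same ratio, so the distortion comes from the unrecorded events and does not require removed women to leave the analysis set.

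**The case against.** The case on the other side has several sound parts.

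- **The illness trigger is narrow.** It is optional and needs both grave illness and intensive care, in a population of healthy singletons of at least 37 weeks already cleared for discharge (2.5). A reader might infer that any readmission or emergency visit leads to removal. The illness clause does not say so; only the physician clause, which has no such threshold, could reach milder cases. The 30% rows above are therefore towards the high end.
- **Cases are not simply lost.** Earlier data are kept, the study must know of the illness in order to act on it, and 6.1 may still capture readmissions within 15 days. This stands. What remains exposed is later events, later outcomes, and details not yet recorded.
- **Section 3.7 does not remove anyone from the analysis set.** A reader might infer that sick dyads leave the denominator and inflate the breastfeeding rate. The text says only that collection ends. Handling of missing outcomes may properly sit in an analysis plan that is not shown.
- **The closing sentence could be meant for the mother's own withdrawal.** That is possible, but it follows the removal clauses without restriction, and 3.7 gives no other data rule for removed dyads.
- **Unsuitability in the 4.1 attrition allowance.** A reader might take it as a licence to exclude women after randomisation. It is part of a sample-size allowance and does not say when it applies. Because 3.2.2 delays randomisation until discharge candidacy is confirmed, it may mean women found unsuitable between consent and allocation. It gives no support to this point.

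**Conclusion.** The point holds as a defect in the data rule. Section 3.7 ends outcome collection for removals that nobody asked for on consent grounds, that happen after randomisation, and that are related to measured outcomes. That undermines the intention-to-treat analysis of all outcomes promised in 4.3 and leaves 3.7 and 6.1 in conflict if both are read literally.

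The effect on the primary outcome is probably small: about 1 point at assumed removal rates of 3% and 1%, well inside the 4.9-point standard error, and none if removal is equal and the true rates are equal. Readmission and safety comparisons are more fragile: about five unrecorded cases in the clinic arm could make equal risks look like a benefit, or hide much of a true excess. This needs removal to differ by arm. Equal shares leave the ratio unchanged, although they still lower the counts and costs. All event and removal rates here are assumptions, since the protocol gives none.

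**What to change.** Reconcile sections 3.6, 3.7, 4.3 and 6.1 as follows:

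1. In 3.7, limit the stop on new data to mothers who withdraw consent for data collection.
2. For any other removal, state that the dyad stays in the intention-to-treat set as randomised, and that outcome collection continues: hospital chart, readmissions and emergency visits, the planned administrative linkage, and the short feeding question where the mother finds it acceptable.
3. State in 3.7 that removed dyads remain in the 15-day readmission review and in the count sent to the monitoring board.

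This concerns data only; when clinic care should stop is a clinical matter on which no rule is proposed here. The cost is a few sentences in the protocol, a line in the consent form, and a small number of extra chart reviews. It should be in place before removals occur, because later analysis cannot restore what was not collected.
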